### Recruitment {15}

Because we are a top hospital in China, we believe we can collect enough patient data within the planned timescale.

## Assignment of interventions: allocation

### Sequence generation {16a}

Each patient will be assigned a computer-generated random number in the central registry.

### Concealment mechanism {16b}

Patients are randomized in a 1:1 allocation ratio either to arm A (RAMPS) or to arm B (SRPS), with a random block size (Fig. 1).

### Implementation {16c}

The central registry in CPGH will generate the allocation sequence, enroll participants and assign participants to interventions.

## Assignment of interventions: blinding

### Who will be blinded {17a}

The experiment was a single-blind trial. Patients will not know their grouping. Surgeons perform operations according to their group.

### Procedure for unblinding if needed {17b}

After the patient is discharged from hospital, we will send the patient’s surgical procedure in the form of medical records.

## Data collection and management

### Plans for assessment and collection of outcomes {18a}

The data manager will use two input methods to enter data from the CRF table into the ResMan database. The inspector will examine each item in the database, report inconsistent result values, validate each item in the original questionnaire, and make corrections as necessary.

### Plans to promote participant retention and complete follow up {18b}

Not applicable.

### Data management {19}

The CPGH will be responsible for data management and statistical analysis in the study. The corresponding tables of codes and informed consent forms will be kept strictly secure in the CPGH file library. All required parameters will be collected in SPSS data files (SPSS version 25, IBM statistics, Chicago, IL, USA).

### Confidentiality {27}

Participants’ medical records will be kept at the hospital. Researchers, research institutions and ethics committees will be allowed access to the records. The study will not reveal the individual identities of the participants. Participants can request access to their personal information (such as address and contact information) at any time and can modify this information if necessary.

### Plans for collection, laboratory evaluation, and storage of biological specimens for genetic or molecular analysis in this trial or for future use {33}

In this trial we will collect blood and drainage fluid samples from patients for laboratory testing.

## Statistical methods

### Statistical methods for primary and secondary outcomes {20a}

Statistical analysts do not participate in clinical observation. They will be blinded to allocation and responsible for statistical analysis of research data and timely delivery of statistical reports to the research director. All analyses will be performed and reported in accordance with the Consolidated standards of reporting trials (CONSORT) statement and the ICH E9 “Statistical Principles in Clinical Trials”. Primary and secondary outcomes will be cross-checked against data. The measurement data are expressed as mean plus/minus standard deviation. The normality test and homogeneity test of variance will be performed first. The independent sample *t* test will be used to compare normally distributed continuous variables, and the values will be represented as the mean with standard deviation. Continuous non-normally distributed variables will be compared using the Mann-Whitney *U* test, and the values will be expressed as the median of the quartile spacing. The categorical variables are compared using the chi-square test or the Fisher’s exact test, and values will be expressed as proportions with corresponding risk ratios and 95% confidence intervals. *P* < 0.05 indicates statistical significance. Statistical analysis will be performed using SPSS 20.0 software.

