### Outcomes {12}

#### Endpoints

The primary efficacy endpoint of the trial will be the rates of resection margins. In the case of malignant pancreatic disease, resection margins are classified by a margin to tumor distance ≥ 1 mm (R0), a margin to tumor distance < 1 mm (R1) or a macroscopically positive margin (R2) [18]. The secondary endpoints are (1) the number of harvested lymph nodes; (2) retrieval postoperative complications including pancreatic fistula, intra-abdominal abscess, and anastomotic leakage, according to the Clavien-Dindo classification (Table 1): complications classified as higher than grade II are regarded as clinically significant [19]; and (3) perioperative indicators; such as duration of the operation, blood loss, blood transfusion volume, rate of transition to open surgery, postoperative hospitalization days, and hospital costs.

**Table 1 Tab1:** Complication grades according to the Clavien-Dindo classication scheme

Grade	Definition
V	Death of patient
IV	Life-threatening complication. Requiring intensive care unit management
IVa	Single organ dysfunction
IVb	Multi-organ dysfunction
III	Requiring surgical, endoscopic, or radiological intervention
IIIa	Intervention not under general anesthesia
IIIb	Intervention under general anesthesia
II	Requiring pharmacological treatment with drugs other than those allowed for grade I complications
I	Any deviation from the normal postoperative course without the need for pharmacological treatment or surgical, endoscopic, and radiological intervention

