### Sample size {14}

Determination of the marginal resection rate is the main endpoint of this study. Published reports describe an R0 resection rate of 50–74% in distal adenocarcinoma in studies with large sample sizes (*n* > 100 patients) [20, 21]. A systematic review of radical antegrade modular pancreatosplenectomy, which identified 13 observational studies involving 354 patients undergoing RAMPS, showed that the R0 resection rate was 88% [22]. According to these studies, we used a two-sided log-rank test, which requires about 23–123 patients in each group with 80% power at the 0.05 level of significance (NCSS and PASS 11 (NCSS Statistical Software, Kaysville, UT, USA)). Considering that there is a large gap in the estimated quantity of samples, we plan to collect 90 samples in each group. Considering a dropout rate of 10%, the total sample size required is 200 patients. After 50 samples have been collected in each group, we will make a mid-term comparison to determine whether there are significant differences between the groups. Based on the results, we decide whether or not to conduct further data collection.

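### Preliminary normality and variance tests on the outcome data decide how each continuous secondary outcome is analysed; one method per outcome should be fixed in advance

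*Protocol article*

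**What the plan says.** All of the rule stands in the protocol article under Statistical methods for primary and secondary outcomes {20a}. It opens with a general statement on reporting, "The measurement data are expressed as mean plus/minus standard deviation", and then sets the preliminary step: "The normality test and homogeneity test of variance will be performed first". Two branches follow. In the first, the independent-sample t "test will be used to compare normally distributed continuous variables, and the values will be represented as the mean with standard deviation". In the second, "Continuous non-normally distributed variables will be compared using the Mann-Whitney" U test, with medians and quartiles reported. The significance threshold is 0.05.

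The section Endpoints, under Outcomes {12}, lists the outcomes this rule governs: number of harvested lymph nodes, duration of the operation, and "blood loss, blood transfusion volume, rate of transition to open surgery, postoperative hospitalization days, and hospital costs". Apart from the conversion rate, these are continuous or counts. No other method is given for any of them.

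The planned size is in Sample size {14}: "we plan to collect 90 samples in each group".

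**The concern.** Three features of the rule cause difficulty.

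- **The estimand follows the data.** Whether the trial reports a difference in means or in medians is settled by a test on the same data that answer the question. A small change in the sample can move an outcome from one branch to the other.
- **The rule is incomplete.** It states nothing that follows from the variance test, and nothing for the case where one arm looks normal and the other does not. The opening statement promises means and standard deviations for all measurement data, which the second branch then contradicts.
- **The rank branch may not answer the cost question.** Costs are commonly right-skewed, and the rule would then compare them by ranks. If the reader wants to know whether one operation costs more per patient on average, a rank test can point elsewhere when the arms differ in spread.

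At stake is the interpretation of the secondary outcomes, above all costs.

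**Working it through.** **Inputs.** From the documents: 90 per arm, 1:1 allocation, threshold 0.05, and the two-branch rule. The rule has no numerical figure of its own to reproduce; the size it works with does reproduce (180/0.90 = 200 patients). The documents give no standard deviation, skewness or cost distribution, so everything below on shape is an assumption. The normality test is taken as Shapiro-Wilk at 0.05, the variance test as Levene, and skewed data as lognormal. Each scenario has several thousand simulated trials (4,000 for the tables in steps 1 and 2).

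**Step 1. How often do the arms disagree on normality, if each arm is tested?** Both arms have the same distribution.

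| Distribution | Arms disagree | Both fail |
|---|---|---|
| Normal | 9% | 0.3% |
| Lognormal, CV 0.1 | 28% | 3% |
| Lognormal, CV 0.2 | 49% | 26% |
| Lognormal, CV 0.3 | 30% | 66% |
| Lognormal, CV 0.5 | 1% | 99% |
| Lognormal, CV 0.8 or more | 0% | 100% |

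The first row agrees with theory: 2 × 0.05 × 0.95 = 9.5%. The gap is large under mild skew and vanishes under strong skew. If a single test is run on the pooled within-arm residuals, the arms cannot disagree; that test rejects normality in 80%, 93% and 98% at CV 0.20, 0.25 and 0.30.

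**Step 2. How often does the variance test fire with no stated consequence?** With normal data, both arms pass normality and Levene rejects in 4% (equal SDs), 45% (SD ratio 1.25) and 85% (SD ratio 1.5). The text still points to a t test here, but does not say whether the equal-variance or the Welch form. With equal arms this matters little: at SD ratio 1.5 with no true difference, both forms reject in 5.1%.

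**Step 3. Does the branch change the result?** With CV 0.20–0.30 and a shift of 0.4 SD, the t test and Mann-Whitney fall on opposite sides of 0.05 in 7–9% of trials.

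**Step 4. Costs.** For a lognormal variable, mean = median × exp(σ²/2), where σ is the log-SD. With equal medians and σ = 0.3 and 0.6, the ratio of means is exp((0.36 − 0.09)/2) = exp(0.135) = 1.145, that is, 14% higher in one arm. The rates below are for each test applied outright, whatever the preliminary test says.

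| Assumed costs, 90 per arm | Mann-Whitney rejects | Welch rejects |
|---|---|---|
| Equal medians, σ 0.3 vs 0.6 (mean 14% higher) | about 6% | about 37% |
| Equal means, σ 0.3 vs 0.6 | about 45% | about 6% |
| Uniform 14.5% shift, σ 0.3 in both | 83% | 83% |
| Uniform 14.5% shift, σ 0.6 in both | 32% | 29% |
| Uniform 14.5% shift, σ 0.8 in both | 19% | 17% |

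Other pairs of unequal spread behave alike. With equal means and CV 0.4 vs 0.7, 0.4 vs 0.8 and 0.5 vs 1.0, Mann-Whitney rejects in 35%, 51% and 61%, and Welch in 4.8%, 5.2% and 6.0%. When the two distributions are identical, Mann-Whitney keeps its level at about 5%. The rank test is therefore valid for what it tests, but it does not track the mean once spread differs.

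**The case against.** The strongest reply is that a rule does exist. It sends variables, not arms, to one of two branches, and it is clear whenever both arms are plainly skewed or plainly normal. Which normality test is used, at what level, and per arm or pooled, are details that a journal article may leave to the full protocol or analysis plan. This stands in part: the disagreement between arms depends on per-arm testing, which the text does not state, and on a window of mild skew that the documents do not give. It does not rescue the rule itself. The article does fix that a preliminary test on the outcome data chooses the analysis, and it does announce a variance test without using it.

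A reader might infer that the rule often leaves the cost analysis without a test. The figures do not support that: with strong skew in both arms the choice is almost never open. The gap in the rule and the handling of costs are separate problems.

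A reader might also infer that a true difference in mean cost is missed by design. That holds only where spread differs between arms and medians are close; under a uniform proportional shift Mann-Whitney does as well as Welch or slightly better. Nor do the documents say that mean cost is the target. Objectives {7} speaks of safety and prognosis, and costs appear only among the perioperative indicators. The cost point is thus an unstated estimand, not a contradiction.

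Finally, the analysts are to be blinded to allocation. This limits choosing a test to favour one arm, though it does not hide p-values, and the documents give no ground to suppose such selection. The two tests also agree at 0.05 in 91–93% of trials in the mild-skew case of step 3.

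**Conclusion.** The concern holds in a limited form. The article lets the outcome data decide the test and the reported quantity for each continuous secondary outcome, and the variance test leads nowhere. These two statements rest on the text alone.

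The sizes rest on assumptions. A disagreement between arms, in about 28–49% of trials, requires per-arm testing and lognormal data with CV 0.1–0.3; it falls to about 1% at CV 0.5. The cost figures require skewed costs, unequal spread between arms, and an interest in mean cost. None of these is stated, though skewed costs are likely.

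One might be tempted to carry the point over to the main result. The documents do not allow that: the R0 rate is categorical and is compared by chi-square or Fisher's exact test with a risk ratio and 95% confidence interval, and the sample size does not depend on this rule. The change is worth making because it costs almost nothing, not because the trial's main conclusion is at risk.

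**What to change.** Delete the preliminary normality and variance tests. Before the outcome data are examined, name one method per continuous secondary outcome, each with an effect estimate and 95% confidence interval. For example:

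- **Operating time and number of harvested nodes:** Welch t test with the difference in means.
- **Hospital costs:** difference in means with a Welch or bootstrap interval, with one sentence stating that mean cost per patient is the quantity of interest. If it is not, state what is.
- **Blood loss, transfusion volume and postoperative stay:** Mann-Whitney test with the Hodges-Lehmann difference. Transfusion volume stays the stated endpoint; replacing it by the proportion transfused would change an endpoint and is not needed.

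Make the general statement on means and standard deviations agree with these choices; medians and quartiles may be shown alongside as description.

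The cost is a few lines of wording, with no added patients or data. The downside is slightly less efficiency for some outcomes if the fixed method proves not to be the best one for the distribution observed.

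### The R0 comparison is valid but unadjusted; a pre-specified model using a tumour measurement from the screening CT/MRI is an optional, modest gain in precision

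*Protocol article*

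**What the plan says.** Under Endpoints: "The primary efficacy endpoint of the trial will be the rates of resection margins", with R0 defined as a distance of at least 1 mm between margin and tumour. The only analysis that applies to it stands under Statistical methods for primary and secondary outcomes {20a}: "The categorical variables are compared using the chi-square test or the" Fisher exact test, and "values will be expressed as proportions with corresponding risk ratios and 95% confidence intervals". No regression, stratified or covariate-adjusted analysis is named there. The section on additional analyses {20b} adds only later subgroups by gender or surgeon. Allocation is 1:1 in blocks of random size, with no stratification factor named.

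Table 2 under Participant timeline {13} marks CT/MRI at Visit 1, the screening visit before surgery. The article does not list tumour size as a recorded variable and does not relate it to R0.

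Sample size {14} gives the planning figures. For conventional surgery: "Published reports describe an R0 resection rate of 50–74% in distal adenocarcinoma in studies with large sample sizes". For RAMPS, a systematic review "showed that the R0 resection rate was 88"%. The calculation is one "which requires about 23–123 patients in each group with 80% power at the 0.05 level of significance", and from that range "we plan to collect 90 samples in each group".

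**The concern.** At the least favourable of its own assumptions (74% versus 88%) the protocol needs 123 patients per group and plans 90, so that is where extra precision would be useful. A covariate that is fixed before allocation and predicts the outcome lowers the variance of the estimated treatment effect without adding a patient. The scan from which one could be taken is already scheduled for everyone, but the stated analysis makes no use of it.

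At stake are a few points of power at the 74% end of the planning range, and an R0 estimate less exposed to a chance difference in tumour size between the arms. The validity of the trial's conclusion is not at stake.

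**Working it through.** **Inputs from Sample size {14}.** Control R0 rate p0 = 0.50 to 0.74; RAMPS R0 rate p1 = 0.88; two-sided alpha 0.05; power 80%; n = 90 per arm.

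**Input not in the article.** The strength of the association between tumour size and R0. I take it as an odds ratio (OR) per standard deviation (SD) of tumour size and show 1.0 (no association) to 2.7.

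**Step 1: reproduce the plan's figure.** Unadjusted two-proportion formula with pooled variance, where p̄ is the mean of p0 and p1:

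n = [1.960 × √(2p̄(1−p̄)) + 0.842 × √(p0(1−p0) + p1(1−p1))]² / (p1−p0)²

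- 50% vs 88%: [1.960 × √0.4278 + 0.842 × √0.3556]² / 0.38² = 22.04, rounded up to 23.
- 74% vs 88%: [1.960 × √0.3078 + 0.842 × √0.2980]² / 0.14² = 122.07, rounded up to 123.

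Both ends match. Although the section says "we used a two-sided log-rank test", the figures come from an unadjusted comparison of two proportions. Sizing and planned analysis therefore agree in being unadjusted.

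**Step 2: unadjusted power with 90 per arm.** Power = Φ((p1−p0)/SE − 1.960), with SE = √[(p0(1−p0) + p1(1−p1))/90].

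- 74% vs 88%: SE = √(0.2980/90) = 0.0575; 0.14/0.0575 − 1.960 = 0.473; power 68.2%. The pooled-variance form gives 67.0%.
- 50% vs 88%: SE = √(0.3556/90) = 0.0629; 0.38/0.0629 − 1.960 = 4.09; power above 99.9%.

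**Step 3: power after adjustment.** Let m0(x) and m1(x) be the R0 probabilities in the two arms at tumour size x. They come from a logistic model with a normal covariate, with the overall rates held at p0 and p1. The large-sample variance of the standardised risk difference d = p1−p0 is

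V = {2E[m0(1−m0)] + 2E[m1(1−m1)] + E[(m1−m0−d)²]} / (2n)

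For 74% vs 88% and n = 90:

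| Assumed OR per SD | Variance ratio to unadjusted | Power | Gain (points) |
|---|---|---|---|
| 1.0 | 1.000 | 68.2% | 0 |
| 1.25 | 0.993 | 68.5% | 0.3 |
| 1.5 | 0.976 | 69.2% | 1.0 |
| 1.8 | 0.952 | 70.3% | 2.1 |
| 2.2 | 0.917 | 71.9% | 3.7 |
| 2.7 | 0.877 | 73.8% | 5.6 |

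In patients, OR 2.2 is worth 90/0.917 − 90 ≈ 8 per arm, and OR 2.7 is worth 90/0.877 − 90 ≈ 13 per arm.

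A simulation of 4,000 trials per setting agrees to within about a point. Unadjusted and adjusted power were 0.678 and 0.697 (OR 1.49), 0.691 and 0.715 (1.82), 0.691 and 0.732 (2.23), 0.676 and 0.737 (2.72). The adjusted analysis rejected in 4.5 to 5.5% of trials with no treatment effect.

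**Step 4: could adjustment restore 80%?** With 90 instead of 123 per arm, the variance would have to fall by 1 − 90/123 = 27%. OR 2.7 gives 12%, and even OR 3.0 gives about 14%.

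**Step 5: chance imbalance.** With 90 per arm, the standard error of the difference in mean tumour size is √(2/90) = 0.149 SD, so a 1.96-SE imbalance is 0.29 SD. That would move the crude risk difference by about 2.4 points at OR 1.8 and 3.8 points at OR 2.7, against a planned difference of 14 points.

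**The case against.** The strongest objection is that nothing here is wrong. An unadjusted two-proportion test is valid under 1:1 randomisation, estimates the marginal risk ratio that the protocol promises, and matches the way the trial was sized. That stands, and the point is therefore only an option. Covariates are also often left to a statistical analysis plan, which is not shown. It could add one, but it would then depart from the analysis this article states.

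A reader might infer that precision is definitely being thrown away. The article does not support that. It neither records tumour size nor links it to R0. The tumour feature it does tie to the margin, in the Background, is invasion of the posterior capsule. The eligibility criteria admit only tumours judged resectable and suitable for robotic resection, which may narrow the range of sizes and weaken any association.

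A reader might also infer that chance imbalance biases the crude estimate. It does not: the shifts in Step 5 are part of the sampling variation that the unadjusted confidence interval already covers. Adjustment narrows that variation; it does not repair a validity problem.

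Finally, the 90 per arm is itself unsettled. Sample size {14} leads to 200 patients in total, whereas Study setting {9} gives 256. With 128 per arm, power at 74% versus 88% is about 82 to 83%. After 10% dropout (0.9 × 128 ≈ 115 per arm) it is about 78 to 79%. The total and the choice of 90 against a requirement of 123 matter more for power than this point, and adjustment resolves neither.

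**Conclusion.** The point holds as an optional efficiency improvement. The stated R0 analysis is valid and unadjusted, and a scheduled pre-surgery scan could supply a covariate that makes it somewhat more precise. At 90 per arm and 74% versus 88%, the gain is about 0 to 6 power points on a base of about 68% for an assumed OR of 1.0 to 2.7 per SD. It is close to nil if size is weakly prognostic (0.3 points at OR 1.25), and at 50% versus 88% there is nothing to gain because power already exceeds 99.9%.

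The figures rest on one normally distributed covariate, a correctly specified logistic model, large-sample variance and 90 analysed patients per arm. It would be wrong to conclude that adjustment makes up for the shortfall against 123 per arm: no association in the range examined brings power to 80%.

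**What to change.** In Statistical methods {20a}, state that the primary R0 estimate comes from a logistic model with arm and preoperative tumour size. Size should be continuous and measured on the Visit 1 CT/MRI before allocation. Standardise the model over all analysed patients to a marginal risk ratio and risk difference with 95% CI. Keep the crude chi-square or Fisher test as a supporting analysis. Standardisation matters because the model's own odds ratio is a conditional measure and would replace the risk ratio that the protocol promises.

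Fix the covariate and model before any comparison by arm, including the interim look at 100 patients. Recruitment has already begun, so for patients already enrolled the size should be read from the pre-surgery scan by someone unaware of arm and margin result.

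Cost: one case report form field from imaging already scheduled, a few lines of analysis text, and code for the standardised estimate and its standard error, which may need software other than the stated SPSS 20.0. No patient, visit or clinical procedure is added.
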